### **3. Methods and Study design**

#### **3.1 Investigational Plan**

Potential research participants are primarily identified through two methods. First, when a patient is diagnosed by the treating surgeon and a specific surgical date is scheduled, the treating physician briefly introduces the research protocol and its objectives to the patient, and inquire about their willingness to participate in the study. If the patient expresses interest and wishes to learn more, the attending physician promptly notifies our research team. Second, as most surgical patients are transferred from the cardiology ward to the cardiac surgery department, our research personnel screen potential candidates for coronary artery bypass graft surgery through the cardiology electronic medical record system. The attending physician notifies our research team upon confirmation of the transfer. Subsequently, the research personnel conduct in-person screening visits with the patients. During the initial screening visits, they comprehensively explain the study's purpose and relevant details, and seek consent from the patient and their family members. Once the patients are determined to be able to comply with the series of assessments and the use of smartphones involved in the study, their eligibility is evaluated based on the study's inclusion criteria. Upon meeting the criteria, the patients or their immediate family members are asked to sign a written informed consent, and are informed of their right to withdraw from the study at any time.

#### **3.2 Inclusion /Exclusion/Drop criteria**

##### **3.2.1 Inclusion criteria**

- (1) Sign the informed consent;
- (2) Patients who plan to undergo isolated coronary artery bypass grafting with general anaesthesia;
- (3) Adults aged  $\geq 18$  years;
- (4) Enrolled participants at least 10 days prior to their surgical procedure.

##### **3.2.2 Exclusion criteria**

- (1) Patients who had a life expectancy  $< 6$  months;
- (2) A history of psychiatric or neurological disorders (including depression, severe central nervous system depression, schizophrenia, epilepsy, and Parkinson's or Alzheimer's disease);
- (3) Significant impairments such as blindness, severe deafness, or dementia that might hinder cognitive

testing;

- (4) Prior use of psychotropic or opioid medications, a previous history of delirium before surgery;
- (5) A documented history of alcohol abuse or withdrawal within the past six months;
- (6) Inability to communicate effectively before surgery due to coma or dementia;
- (7) Ongoing participation in another clinical trial;
- (8) Planned re-operation within seven days of the first.

### 3.2.3 Drop criteria

- (1) Patients who died before the primary outcome assessment;
- (2) Those who do not have any monitoring records or whose CRF records are incomplete;
- (3) Surgeons changed the operation plan
- (4) Patients who quit the research;

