## 4.2 Statistical methods

### 4.2.1 Data set

Modified intention-to-treat analysis (m ITT) was defined that patients were primarily analyzed within the groups to which they were assigned, whether or not the minimum compliance threshold of training was met, excluding those without any record of follow-up or cancelled surgeries. Primary indicators are analyzed according to the m ITT principle.

Per protocol set (PPS) refers to the set of cases that meet the minimum compliance threshold of training, have completed the treatment protocol. The PPS is a subset of the ITT in which each subject in the dataset is a valid case or sample with good adherence, no protocol violations, and complete baseline values for key indicators.

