### 4.2.3 General considerations

**Data set:** The assessment of primary endpoint will be performed based on m ITT set. The per protocol set is mainly used for sensitivity analysis. Patients who engaged in cognitive training for 3 or more hours were considered to have met our minimum compliance threshold, and included in per protocol set. The establishment of this threshold is derived from the results of our preliminary meta-analysis.

**Covariates and subgroup analysis:** Subgroup analysis will be performed and the subgroup analysis will be carried out as exploratory. To evaluate treatment effect heterogeneity on the primary outcome, predefined subgroup analyses were performed based on surgical methods, age, sex, education level, and baseline cognitive function. Interactions between cognitive training and each variable were assessed by adding interaction terms to the logistic regression model.

**multi-center effect analysis:** This is a multicenter RCT study, and there may be center effects among different centers. The logistic regression models will be used to control the multi-center effect, with the different centers set as fixed effect.

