#### **General analysis:**

The data analyses mainly include statistical description and statistical inference. Quantitative data will be described by central tendency and dispersion tendency. The normally distributed data of central tendency and dispersion tendency will be described as means and standard division, respectively. The non-normally distributed data of central tendency and dispersion tendency will be described as median and quartiles. The qualitative data will be described as frequency and percentage. Statistical inference,

independent t test or non-parameter test will be used to compare the quantitative data between the two groups, while chi-square test or Fisher's exact test will be used for comparing the qualitative data between the two groups.

For missing data, imputation techniques were used. Statistical analyses were performed using SPSS 23.0 (IBM SPSS) and R (R software 4.2.1), and 2-sided  $P < 0.05$  was considered to be statistically significant in all statistical tests.

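### The drop criteria (3.2.3) and the mITT definition (4.2.1) disagree on which randomised patients are analysed; applying 3.2.3 to the analysis could bias the primary comparison and would omit early deaths.

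*Protocol*

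**What the plan says.** Section 3.2.3 of the protocol names four grounds for dropping a patient. The first is early death, worded as "Patients who died before the primary outcome assessment". The second concerns data completeness and reads "Those who do not have any monitoring records or whose CRF records are incomplete". The third is an altered operation and the fourth is withdrawal from the study, put simply as "Patients who quit the research".

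Section 4.2.1 defines the mITT set differently. On group membership it says "patients were primarily analyzed within the groups to which they were assigned, whether or not the minimum compliance threshold of training was met". The only exclusions it then allows are given as "excluding those without any record of follow-up or cancelled surgeries". Section 4.2.3 makes this the primary set: "The assessment of primary endpoint will be performed based on m ITT set".

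Two other places bear on the point. Under General analysis in 4.2.3 the protocol says "For missing data, imputation techniques were used". Section 3.7.3 lists 30-day all-cause mortality as a secondary outcome and gives a patient who dies within 30 days of surgery a DAOH30 of 0.

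**The concern.** The two lists overlap only in part, and no sentence says which one governs the analysis. Membership of the primary analysis set is therefore open for some patients, and could be settled after data are seen.

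All four drop criteria can operate after randomisation. Enrolment is at least 10 days before surgery (3.2.1), and the envelope is opened immediately after enrolment (3.5). Patients know their allocation (3.5) and only one arm carries the training load (3.3.2), so withdrawal in particular could differ between arms. Excluding such patients gives up the protection of randomisation for the delirium comparison. Excluding early deaths takes events out of an outcome that is meant to count them.

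**Working it through.** **1. How each section classifies the same patient**

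| Patient | 3.2.3 | mITT in 4.2.1 |
|---|---|---|
| No follow-up or monitoring record at all | dropped | excluded |
| Operation cancelled | dropped, if read as a changed plan | excluded |
| Operation changed but performed | dropped | kept |
| Some follow-up, CRF partly filled | dropped | kept |
| Quits after some follow-up | dropped | kept |
| Dies in the day 1–7 window after some assessments | dropped, if the assessment means the whole window | kept |

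The first two rows agree closely enough. The last four conflict.

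The last row depends on an undefined term. If the primary outcome assessment means the first postoperative CAM, an early death has no delirium data and may fall under the no-follow-up exclusion anyway. If it means the end of the day 7 or discharge window, a patient delirious on day 2 who dies on day 4 loses a recorded primary event.

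**2. Conflicts with other rules**

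- Imputation (4.2.3) presupposes that incomplete records stay in. Dropping every incomplete CRF leaves little to impute.
- Mortality and DAOH30 (3.7.3) need early deaths in the data, as an event and as a score of 0.

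**3. The plan's own figure**

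Section 4.1 uses 35% versus 17.5% (a 50% relative reduction), two-sided 0.05 and 80% power. With unpooled variance:

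n = (1.960 + 0.842)² × (0.35×0.65 + 0.175×0.825) / 0.175² = 95.3, so 96 per arm.

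Allowing for 10% dropout, 96/0.9 = 106.7, so 107 per arm and 214 in total. Both stated figures reproduce. The inflation treats dropouts as patients who will not be analysed.

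**4. Illustrative effect on the primary comparison**

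Assume no true effect: 35% in both arms, 107 per arm, 0.35 × 107 = 37.45 expected cases. If d patients per arm are dropped and a fraction f of them were delirious, then

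observed risk = (37.45 − d×f) / (107 − d).

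The protocol gives neither d nor f. Here d = 11 uses the whole 10% allowance and d = 5 roughly half of it. The values f = 60% in one arm and 35% in the other are assumed.

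| d per arm | Risk with f = 60% | Risk with f = 35% | RR if the 60% is in the training arm | RR if the 60% is in the routine-care arm |
|---|---|---|---|---|
| 11 | 30.85/96 = 32.1% | 33.6/96 = 35.0% | 0.92 | 1.09 |
| 5 | 34.45/102 = 33.8% | 35.7/102 = 35.0% | 0.97 | 1.04 |

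**5. Illustrative effect on 30-day mortality**

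The protocol gives no mortality rate. Assume 2% of 214, which is 4.28 deaths. If half are early and dropped, the rate among those left is 2.14/211.86 = 1.0%. With 25% to 75% of deaths early, it reads 1.5% to 0.5%. With half early, assumed true rates of 1% and 3% read 0.5% and 1.5%. The understatement follows by construction wherever early deaths are left out.

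**The case against.** The best defence is that 3.2.3 never says dropped patients leave the analysis. It stands beside the eligibility criteria, while 4.2.1 is the specific rule on analysis sets and 4.2.3 names mITT as primary. If the specific rule governs, there is no completer analysis. Likewise, no text applies the drop criteria to secondary outcomes, and 3.7.3 plainly means deaths to count in DAOH30.

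This limits the point but does not remove it. CRF completeness is a data condition, and death is not a reason to stop a procedure, so removal from analysis is the natural reading of those criteria. The sample-size inflation also treats dropouts as lost. Nor can 3.2.3 be taken as the per-protocol rule, since 4.2.1 defines that set separately without referring to it. Both rules stand in the protocol itself, so this is not a detail left to a separate SAP.

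Three further objections stand:

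- Surgeons, anaesthesiologists and outcome assessors are blinded (3.5). A changed operation or a gap in outcome records is therefore less likely to depend on arm. Differential withdrawal is the main route to bias.
- The 10% allowance must also cover cancelled surgery and absent follow-up, which both lists remove. The disputed number is therefore below 11 per arm, by an unknown amount.
- A reader might infer that the plan does bias the primary result in favour of training, and might show it with steeper splits of delirium among the dropped, such as 80% versus 20% or 100% versus 0%. The protocol supports neither the direction nor those splits.

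**Conclusion.** The contradiction is real. The protocol gives two incompatible answers to who is in the primary analysis, and one of them also conflicts with its imputation statement and its definitions of 30-day mortality and DAOH30.

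Bias in the primary result is a risk, conditional on 3.2.3 being applied to the analysis. Its size and direction cannot be fixed from the protocol. Under the assumed split of 60% versus 35%, the spurious risk ratio is about 0.92 to 0.97, or 1.04 to 1.09 the other way. That is small beside the planned risk ratio of 0.50, but it comes on top of whatever the true effect is. On the same condition, with criterion 1 read as covering the whole day 7 or discharge window, the loss of early deaths from mortality and DAOH30 is certain in direction and unknown in amount.

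It should be settled before analysis because it concerns membership of the primary analysis set.

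**What to change.** - State that 3.2.3 governs only the stopping of study procedures and that 4.2.1 alone defines the analysis set.
- Keep in mITT every randomised patient whose operation took place and who has any follow-up record, whatever the change of plan, withdrawal or CRF completeness. For withdrawals, use data up to withdrawal where consent allows. The existing exclusions for no follow-up and cancelled surgery can stay.
- Count all deaths in 30-day mortality and DAOH30.
- For death before day 7, count any delirium recorded before death as a primary event, and add a sensitivity analysis of delirium or death.

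The cost is a wording change, some imputed outcomes and one extra sensitivity analysis. The sample size is unaffected.

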## 3.3 Research device and procedures

### 3.3.1 Research device

| Name                              | Manufacturer                                        | Details                                             |
|-----------------------------------|-----------------------------------------------------|-----------------------------------------------------|
| Android mobile phone              | Redmi 9A Xiaomi Technology Co. LTD                  | Internet-connected, with a 6.5-inch-diagonal screen |
| Application "The Light of Future" | V 4.13.1, Beijing Entelligence Technology Co., Ltd. | Offers a range of online games                      |

### 3.3.2 Cognitive training group

Patients randomized to cognitive training were given an internet-connected Android mobile phone with a 6.5-inch-diagonal screen. The phones were loaded with a dynamic cognitive exercise mobile application ("The Light of Future", v4.13.1, Beijing Entelligence Technology Co., Ltd.) that offers a range of online games designed to engage and challenge cognitive abilities including memory, imagination, reasoning, reaction time, attention, and processing speed.[40] Tasks and their difficulty were initially tailored to patients' age and educational level with the goal of balancing cognitive stimulation and enjoyment. Thereafter, task difficulty was automatically adjusted based on users' performance with the goal of keeping the challenge level within a zone that promoting adherence to the training program while preventing excessive psychological burden and emotional distress associated with overly difficult tasks. The software developer has generously provided 200 complimentary redemption codes that grant access to all games in the "The Light of Future" when redeemed. Each patient has been allocated a unique redemption code, which, when matched with the corresponding patient, enables the technical staff of the software developer to capture all background information during the training process.

The initial step involves entering the patient's baseline information (i. e. age, gender and educational level and so on) into the software. Before the formal training begins, the research staff

explain the operational procedures and guidelines of the software to the patients. Additionally, we select an example game from each cognitive domain to guide the patients on the effective usage of the software. After receiving the instructions, patients are required to independently play six games, each representing a cognitive domain, to assess their proficiency and completion. Formal cognitive training begins only after patients have achieved a basic proficiency level in using the software games. After the first day of training, the research staff meticulously assess the patients' performance to identify any deficiencies or incorrect actions. If found, the research staff promptly inform and rectify them.

Patients were instructed to spend 10 hours on cognitive training. We asked patients to spend at least a full hour per day, over two or three sessions, and that daily sessions include at least one game from each of the six available cognitive domains, more as time permits. A minimum of 10 days of training prior to surgery is needed, equaling a preoperative exercise dose of at least 10 hours. The patients were systematically guided to complete cognitive games in each domain successively. After finishing a game in one cognitive domain, they immediately moved to the next one, and this sequential training ensured that each patient underwent comprehensive exercises in 6 cognitive domains. Participants were free to choose the timing of each training session. The Light of Future software will ensure that each patient is exposed to the same set of games.

Considering that each game includes a tutorial of several tens of seconds, and patients may potentially linger in a game due to various reasons without actively participating but still being automatically timed. Hence, it is necessary to distinguish between the actual in-game time and time spent outside of the game. Because each game is limited by a countdown timer, with each game lasting approximately 58 seconds. We consider the time spent lingering in a game for over two minutes with a completion rate of less than 50%, and those abruptly quitting before reaching 50% completion as invalid training time. If a patient exits a game midway after exceeding 50% completion, the actual effective training duration is calculated based on the completion percentage generated within that game. Additionally, when calculating the actual in-game participation time, we exclude the tutorial time at the beginning of each game.

Details of each participant's use was recorded by the Light of Future application, including which games were used, when and for how long, and participants' success with each. At the end of each day's training, the researchers collect the devices and calculate the actual effective training duration for the patients based on detailed backend information. The total training duration is computed by summing up all the training durations the day before the surgery. The final record of the total training duration is in hours (recorded as an integer). For instance, if the total duration is more than 6 hours but less than 7 hours, it is recorded as 6 hours. The evening prior to the surgical procedure, the researchers will comprehensively collect the equipment and complete the collection of all training data. The patient will be unable to participate in any cognitive training.

### **3.3.3 Routine care group**

Participants assigned to routine care were provided with standard hospital attention without any specific cognitive training.

### **3.4 Randomization Procedure**

Patients were assigned by computer to either cognitive training or routine care in a 1:1 ratio stratified by

study site with random blocking. The computer-generated randomization schema was developed by an unblinded statistician and allocation was concealed from study investigators in sequentially numbered sealed opaque envelopes.

### **3.5 Blinding**

Investigators who provided preoperative cognitive training opened randomization envelopes immediately after eligibility assessment and formal trial enrolment. Patients were not blinded as they needed to adhere to the protocol. However, surgeons, anaesthesiologists, statisticians, and members of the study team responsible for assessing neurocognitive function and postoperative clinical outcomes were unaware of the patient allocation or treatment.

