### **2.1Primary Aim**

To evaluate the extent to which preoperative in-hospital cognitive training reduces delirium in patients recovering from coronary artery bypass grafting surgery.

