### **3.7.3 Postoperative outcomes**

#### **The primary outcome:**

The incidence of delirium from postoperative day 1 to postoperative day 7 or before discharge, whichever occurred first.

Diagnosis of POD was based on the results of CAM or CAM-ICU twice daily, [42,43] specifically from 08:00 to 10:00 and from 18:00 to 20:00. All blinded researchers were trained in CAM/CAM-ICU assessment and the consistency among research members was reached. When there is a contradiction between the diagnosis obtained by the scale and the diagnosis of the psychiatrist, when there are still differences after consultation, the diagnosis of the psychiatrist shall prevail. In order to prevent missed diagnosis, we should communicate with the medical staff in the ward in time. After the patient is selected, the family member or escort staff should be informed, and the investigator should be informed of the evaluation of delirium in time when any abnormal performance of the patient's mood, consciousness, cognition and so on is found. Comprehensive reviews of progress notes, nursing documents, and medical records were conducted by blinded investigators to identify instances of delirium between postoperative day 1 and 7, employing a chart-based delirium identification instrument. [44,45] Patients diagnosed with delirium through any of the aforementioned methods were considered to have experienced delirium on that particular day. When postoperative delirium is found, the subject should communicate with the competent physician and decide on further diagnosis and treatment. If the patient's performance was normal 7 d after operation, the visit ended, while the patient with continuous delirium was followed up

until normal or discharged.

Outcomes were assessed by investigators specifically trained in recognition and assessment of delirium.

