**Secondary outcomes:**

- (1) cumulative incidence of POD
- (2) incidence of severe delirium, evaluated with the Memorial Delirium Assessment Scale (MDAS)[46]
- (3) postoperative cognitive dysfunction (POCD) on postoperative day 7 or at discharge if earlier, used by the Montreal Cognitive Assessment (MoCA) (range, 0 [worst] to 30 [best]), defined as a 1 standard deviation decrease from baseline in Montreal cognitive assessment score at postoperative day 7 or discharge.
- (4) cognitive function one month after surgery, used by the Revised Telephone Interview for Cognitive Status (TICS-m) (range, 0 [worst] to 50 [best])
- (5) 30-day all-cause mortality
- (6) durations of intensive care unit (number of days in the intensive care unit from the end of operation to discharge) and postoperative hospital care.
- (7) elapsed time from the end of surgery to delirium onset
- (8) duration of delirium (defined as the period between the first and last delirium-positive day, even if there were non-delirious days in between)
- (9) the total number of delirium-positive days in patients who developed delirium
- (10) cognitive function at three time points (baseline, preoperative, postoperative day 7 or at discharge if earlier. was used to assess early POCD on the seventh day after surgery or at discharge and cognitive function at any time points before or after surgery.
- (11) Postoperative intubation time, defined as duration from the end of the procedure to extubation.
- (12) intensive care unit readmission within 30 days after surgery.
- (13) Number of days alive and out of the hospital within 30 days. (The sum of the number of days patients were alive and not in the hospital within 30 days after surgery. It is calculated as 30 days minus the total number of days in hospital after surgery (maximum 30 days, minimum 0 days). If the patient is not hospitalized from 00:00 to 24:00 in a day, the number of days without hospitalization can be counted; After discharge, patients were hospitalized for a second time, and the second hospitalization time was also included in the total number of days in hospital. The patient died within 30 days of surgery. DAOH 30 is 0 days; If the patient was not discharged 30 days after surgery, DAOH 30 was recorded as 0 days.)

All outcomes were assessed by investigators masked to patient allocation.

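### Section 3.5 does not say whether ward and ICU staff are masked, although chart review of routine notes can yield a primary-outcome event without a positive CAM or CAM-ICU

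*Protocol*

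**What the plan says.** **Who is masked.** Section 3.5 names the roles: "surgeons, anaesthesiologists, statisticians, and members of the study team responsible for assessing neurocognitive function and postoperative clinical outcomes were unaware" of the allocation. It also says "Patients were not blinded as they needed to adhere to the protocol". Ward nurses, ward physicians and ICU staff are not mentioned in either direction.

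**What the training looks like.** The primary aim (section 2.1) is to find out how far "preoperative in-hospital cognitive training reduces delirium in patients recovering from coronary artery bypass grafting surgery". Section 3.3.2 says "A minimum of 10 days of training prior to surgery is needed", with at least an hour a day in two or three sessions on a phone supplied by the study. Staff instruct the patient beforehand and check performance after the first day, and at the end of each day's training "the researchers collect the devices and calculate the actual effective training duration for the patients". All equipment is taken back on the evening before surgery. Under section 3.3.3, controls receive usual hospital care with no sham activity.

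**How a primary event arises.** Section 3.7.3 uses CAM or CAM-ICU twice daily by blinded researchers. It adds a second source: "Comprehensive reviews of progress notes, nursing documents, and medical records were conducted by blinded investigators to identify instances of delirium", using a chart-based instrument. A positive result by any of the methods makes that day a delirium day. The secondary-outcome list closes with "All outcomes were assessed by investigators masked to patient allocation".

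**The concern.** Masking the person who reads a chart does not mask the person who wrote it. A chart instrument can classify only what was recorded, and recording confusion depends on who is watching and what they choose to write down. If some authors of the postoperative notes know which patients were trained, and record less confusion in those patients or more in the others, the difference passes through the blinded reviewer into the primary outcome. It would favour the trial's hypothesis.

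The only sensitivity set stated in the protocol is the per protocol set (section 4.2.3), defined by hours of training. It uses the same any-method outcome and so cannot separate chart-only events from events that the masked assessors found themselves.

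**Working it through.** **Step 1. The route, read from the text.**

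| Link | Source | Status |
|---|---|---|
| Training is in hospital, daily, for at least 10 days | 2.1, 3.3.2 | stated |
| Controls have no sham; patients know their arm | 3.3.3, 3.5 | stated |
| Preoperative ward staff could see who trains | follows from the two rows above | inference |
| ICU staff see the training | 3.3.2: equipment removed the evening before surgery | not supported |
| Ward and ICU staff are masked | 3.5 | not stated |
| Routine notes feed the primary outcome | 3.7.3 | stated |
| A chart-identified event counts without a positive CAM/CAM-ICU | 3.7.3, any-method rule | stated |
| Staff who saw training also write notes on days 1 to 7 | nowhere | plausible, not stated |

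The route is open on the text. Whether it is used depends on the inferred and unstated links.

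**Step 2. The plan's own sample size (section 4.1).** Inputs: 35% against 17.5%, two-sided alpha 0.05, power 80%, 1:1. With the unpooled normal formula:

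n = (1.960 + 0.842)² × (0.35×0.65 + 0.175×0.825) / 0.175² = 7.849 × 0.371875 / 0.030625 = 95.3, rounded up to 96.

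Dropout: 96 / 0.90 = 106.7, rounded up to 107 per group and 214 in total. Both figures reproduce, and this point does not affect them.

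**Step 3. Illustration of size.** The documents give no rate of chart-only events and no difference between arms, so the difference d is an assumption. Take no true effect, a rate p in the training arm, p + d in controls because of extra chart-only events, and n = 96 per arm. The chance of a two-sided P < 0.05 is

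Φ((d − 1.96·SE0)/SE1) + Φ((−d − 1.96·SE0)/SE1),

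where SE0 uses the pooled rate and SE1 the two separate rates.

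For p = 0.30 and d = 0.05:
- SE0 = √(2×0.325×0.675/96) = 0.0676
- SE1 = √((0.35×0.65 + 0.30×0.70)/96) = 0.0675
- first term: Φ((0.05 − 0.1325)/0.0675) = Φ(−1.222) = 0.111
- second term: Φ(−2.703) = 0.003
- total: 0.114

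| Assumed excess in controls (points) | Base rate 30% | Base rate 35% |
|---|---|---|
| 0 | 5.0% | 5.0% |
| 2 | 6.0% | 6.0% |
| 3 | 7.3% | 7.2% |
| 5 | 11.4% | 11.0% |
| 8 | 21.5% | 20.5% |

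Only a difference in charting between the arms produces this inflation. Equal over-recording in both arms would leave the null error rate at 5%.

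**The case against.** The strongest reply is that the protocol protects this endpoint better than a quick reading suggests.

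- **ICU exposure.** A reader might infer that ICU clinicians watch the training. They do not: the phones are gone by the evening before surgery. Section 1 places typical onset at 24 to 72 hours after surgery, so the main risk period comes after every visible sign of allocation has been removed. ICU staff could learn the arm only second-hand. This stands.
- **Notes alone.** A reader might infer that a nurse's note by itself makes a case. A blinded investigator must first classify the record with a chart-based instrument. This stands, although the classification still depends on what the author wrote.
- **Unmasked observers.** It is tempting to say that the endpoint rests on unmasked observers. The protocol is silent on these roles and does not call them unmasked. It states that surgeons, who may write some of the progress notes, were unaware. Nor does it say that staff who saw the training wrote the postoperative notes. This stands.
- **The general masking statement.** A reader might call "All outcomes were assessed by investigators masked to patient allocation" false. It describes assessors and agrees with sections 3.5 and 3.7.3; it makes no claim about who wrote the source records. It needs no rewording.
- **Size.** Chart-only events are those missed by trained assessors visiting twice a day. An 8-point differential within that residue would be nearly half the planned effect (8/17.5 = 46%), and nothing in the document supports it. Differences of 2 to 3 points move the error rate only to about 6-7%. This is a fair limit on the concern.
- **Place.** A CAM-only analysis could sit in a separate SAP that is not shown, so its absence here is not proof that none is planned. The list of masked roles and the any-method rule, however, are fixed in this protocol, and together they create the route.

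**Conclusion.** The point holds in a limited form. The protocol does not state masking for ward and ICU staff. Preoperative ward staff could see the training, and the any-method rule admits primary events that rest on routine notes without a positive CAM/CAM-ICU. Such chart-only events may therefore depend on authors who knew the arm.

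The text does not show that this happened, that ICU staff saw the training, or that any masking statement is untrue. The size of any bias is unknown. With 96 per arm, a 30% base rate and no true effect, an assumed 3- to 5-point excess of chart-only events in controls would raise the false-positive rate from 5% to about 7-11%. That range depends entirely on the assumed differential. This is a cheap improvement and does not call for a change of design, sample size or primary definition.

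**What to change.** Keep the primary definition. Then:

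1. Pre-specify a sensitivity analysis of the primary outcome that counts only events found by the masked twice-daily CAM/CAM-ICU, and report the number of chart-only events by arm. If the two analyses agree and chart-only events are few or balanced, the concern is largely answered.
2. Give chart reviewers only the notes from postoperative days 1 to 7, with any mention of training or the study phone removed.
3. State in section 3.5 the masking status of ward and ICU staff.

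**Cost.** The analysis uses data already collected, provided the method that identified each event is recorded. It will have fewer events and somewhat lower sensitivity, because chart review also picks up delirium between visits; it should therefore support the primary analysis and not replace it. Redaction takes a little work.
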